# Blended Care Intervention for Cancer Aftercare in General Practice Centers: Protocol for a Randomized Controlled Trial

**DOI:** 10.2196/64662

**Published:** 2025-02-12

**Keywords:** cancer aftercare, general practice, blended care, eHealth, randomized controlled trial, cost effectiveness, general practitioners, online intervention

## Abstract

**Background:**

Combining effective eHealth programs with face-to-face consultations in general practice may help general practitioners care for survivors of cancer.

**Objective:**

This study protocol describes a 2-armed randomized controlled trial to evaluate the cost-effectiveness of a blended intervention integrating the Cancer Aftercare Guide in general practice centers (GPCs).

**Methods:**

A parallel-group design will compare an intervention group with a waiting list control group. Participants will be nested within GPCs and randomization will occur at the GPC level. The participants in the intervention group will receive a blended care intervention. In contrast, the participants in the waiting list control group will receive care as usual for the duration of this study and will receive the online intervention afterward. All participants will be asked to complete an online questionnaire at baseline, 6 months, and 12 months after baseline, measuring self-reported adherence to lifestyle recommendations, psychosocial well-being, and quality of life. A process evaluation and cost evaluation are also included in this study. The effects will be evaluated based on differences in residual change scores between intervention and control group participants, using multilevel linear regression analyses. Moreover, effect analyses will be supplemented with Bayes factor analyses. Finally, an economic evaluation will be conducted from a societal perspective and will include medical costs, productivity costs, and costs of the blended care intervention.

**Results:**

This study was funded in July 2020. Data collection started in August 2022 and is likely to be completed by April 2025. As of December 2024, a total of 127 participants have been included in this study, recruited across 26 GPCs in the Netherlands. Data analysis will commence once data collection is completed. Data analysis is estimated to start in the spring of 2025. The results will likely be published in 2026.

**Conclusions:**

The results will provide insight into the effectiveness of blended care and may be relevant to cancer aftercare, general practice, and the field of eHealth implementation in general. Potential challenges lie in recruitment due to the strain on the health care system since the COVID-19 pandemic.

**Trial Registration:**

ISRCTN ISRCTN12451453; https://www.isrctn.com/ISRCTN12451453

**International Registered Report Identifier (IRRID):**

DERR1-10.2196/64662

## Introduction

In the coming decades, the growing number of survivors of cancer will challenge health care worldwide. Global data show the increased incidence and survival rates, indicating an increase in the number of survivors of cancer worldwide [1]. Data for the Netherlands (total population of 17 million) predict that in 2032, a total of 1.4 million people will be receiving treatment for cancer or will have been successfully treated for cancer [2]. This underlines the urgency of studying the needs of survivors and finding ways to meet these needs to safeguard the quality of life (QoL) after disease and treatment.

After treatment, survivors of cancer may face physical, psychological, and psychosocial challenges that affect their transition to normal life. In addition, survivors of cancer must adhere to lifestyle recommendations regarding physical activity (PA), diet, smoking cessation, and alcohol consumption to prevent recurrence or the development of comorbidities [3]. In reality, however, many survivors of cancer find it difficult to adhere to these guidelines [4]. They seek support to help them recover and cope with the effects of their disease [5]. However, due to a shortage of health care professionals and increasing demand for care in the general population due to aging, survivors of cancer may not always receive the support they need.

Over the past decades, several eHealth interventions have been introduced to support survivors of cancer in their healthy recovery. The online Cancer Aftercare Guide (CAG) is an example of such an intervention [6,7]. The CAG is a web-based eHealth intervention that targets lifestyle and common psychological and psychosocial problems experienced by survivors by promoting self-management of these problems using evidence-based techniques, such as cognitive behavioral therapy and problem-solving therapy. Effectiveness evaluation has shown that the CAG is effective in reducing fatigue, depression, and anxiety and in increasing PA and healthy eating [8-11]. This shows that the CAG can help survivors cope with common cancer-related problems and can help reduce the risk of future disease by promoting a healthy lifestyle.

The use of eHealth for applications such as disease management and patient data sharing is encouraged [12,13], but in reality, effective eHealth interventions struggle to reach their target population [7,14,15]. For survivors of cancer in particular, it has been found that while they use the internet to search for health information, their use of eHealth self-help programs is not common [16]. One reason for this may be that many eHealth interventions are not implemented in everyday practice [17]. To improve the use of eHealth, the Dutch eHealth Monitor suggests that health care providers play an important role in informing patients about eHealth self-help programs and that health care workflows should be designed to facilitate the use of eHealth through blended care [18]. Similarly, in the case of the CAG, Willems et al [11] and Kanera [6] state that the online intervention could be offered in a blended approach, where patient-therapist interaction is provided, to promote patient engagement with the intervention.

Apart from a biyearly follow-up aimed at detecting recurrence, no structural care is currently provided for survivors of cancer in the Netherlands. For issues related to cancer survivorship, patients are referred to their general practitioner (GP) [19], resulting in on-demand care requests. In addition, GPs are responsible for tertiary prevention, which targets healthy lifestyle behaviors in survivors of cancer. With the increasing number of survivors of cancer, this demand will pose a significant challenge to general practice workflows. Therefore, a structured approach is essential for GPs to meet the needs of their patients. This is illustrated by the Dutch College of General Practitioners (in Dutch: *Nederlands Huisartsen Genootschap*), which stated that general practice could structurally provide cancer aftercare [20]. Implementing the CAG in general practice in a blended care setting could provide a solution to the growing demand for cancer aftercare by promoting healthy recovery and improving self-management of problems, ultimately reducing the care needs of survivors of cancer.

This study protocol outlines a randomized controlled trial (RCT) to investigate the cost-effectiveness and associated process evaluation of a blended care approach offering the CAG in general practice. The blended care intervention has been co-designed with GPs, practice nurses (PNs), and survivors in a separate study ([name], unpublished data, 2025) and has been tested in a pilot study before starting this RCT.

## Methods

### Study Design

An RCT will be conducted to compare the effectiveness of the blended CAG intervention between the intervention group and the waiting list control group. A general practice center (GPC) is usually run by at least 1 GP, supported by one or more medical assistants. In addition, many Dutch GPs are supported by PNs who are dedicated to patients with chronic disease, older adult care, and mental health care. The PNs provide additional care for identified health problems, such as asthma, chronic obstructive pulmonary disease, and diabetes (for the somatic nurse) or mental health problems (for the mental health nurse). The intervention protocol is implemented by either the GP or the PN (under the supervision of the GP). A full list of participating GPCs can be requested from the researchers.

### Recruitment of GPCs

GPCs will be recruited through a variety of channels, including calls published in online primary care newsletters distributed by Regional Collaborative Care Groups or special interest groups dedicated to oncology care or lifestyle counseling in primary care. In addition, direct mail will also be sent out by the research team. If no response is received within 4 weeks, the direct mailing will be followed by telephone calls to discuss potential participation. GPCs are eligible to participate if they are located in the Netherlands. If the GPC agrees to participate in this study, an appointment will be made for the researcher to visit the GPC to give instructions on this study protocol.

### Recruitment of Participants

#### Overview

Survivors of cancer will be recruited by general practice personnel (GPP: either GP, PN, or assistants). From the GP’s electronic medical record (in Dutch: *Huisartsen Informatie Systeem*), the GPP will select patients who meet the following inclusion criteria: (1) patients who have completed primary treatment of cancer (eg, radiotherapy, chemotherapy, or surgery), with the last treatment having been between 6 weeks and 3 years ago, or who belong to a watchful waiting condition (eg, option for prostate cancer patients); (2) patients who are 18 years of age or older; (3) patients who are able to read and speak Dutch; (4) patients without a serious medical, psychiatric, or cognitive condition that would interfere with participation; (5) patients who have access to the internet and at least minimal experience of using it; and (6) patients who have access to a computer or a tablet.

If desired, the selection of participants can be assisted by the researcher (under the supervision of the GP).

Eligible patients will be invited to participate in this study using an invitation package distributed by the GPC. The information package consists of an information letter, an informed consent form (Multimedia Appendix 1), and a prepaid return envelope. Survivors of cancer who agree to participate will need to sign the consent form and return it to the research team with the return envelope. The researchers will notify the GPC when the consent form has been received and stored. Enrolled patients will receive a welcome email from the researchers, informing them of their randomization (intervention or control group) and providing a link to the first online self-report questionnaire (baseline measurement). Awareness of randomization can lead to selection bias, but studies on survivors of cancer have shown that this effect is minimal [8-11]. Informing patients about the group to which they are assigned is required in the Netherlands by the Medical Research Involving Subjects Act.

#### The CAG Intervention

The online CAG program provides personalized information in 8 modules covering healthy lifestyles and common psychosocial issues related to cancer survivorship (ie, PA, diet, smoking cessation, alcohol use, fatigue, anxiety and depression, return to work, and social relationships). The CAG will use data from the baseline assessment to create the Module Referral Advice (MRA; Multimedia Appendix 2). The MRA presents personal outcomes across the 8 subtopics featured in the CAG and advises the participant to visit the module that corresponds to their greatest need, as indicated by the MRA. The modules consist of textual information and advice, video clips (in which former cancer patients share their survivorship experiences), and tasks or exercises that the participants can complete independently.

#### Intervention Procedure

Participants in the intervention group will receive the CAG blended care intervention. This means that after completing the baseline measurement, they will be given access to the online CAG. Participants will use the online CAG program independently at home. In addition, they will be invited to 2 consultations with their GP or PN. Within the online CAG, the intervention group participants will receive personalized advice on 8 topics related to cancer survivorship based on their results at baseline. This is represented by the MRA. Participants are asked to share their MRA results with the GP or PN at their first consultation. During the first consultation, the GP or PN and the participant will discuss the MRA results. Through shared decision-making, the GP or PN will motivate the participant to choose at least 1 of the 8 subtopics to focus on for the next 4 to 6 weeks, after which the follow-up consultation will take place. During the follow-up consultation, the GP or PN will enquire about the participant’s progress with the chosen topic or topics. Any questions or problems the participant may have in interpreting the (lifestyle) advice given by the program will be addressed in the personal consultation. After the follow-up consultation, the participant will retain access to the online CAG intervention for up to 6 months after the start of the baseline measurement.

After completing the baseline measurement, participants in the control group are directed to a message thanking them for completing the questionnaire, asking them to log out and return only for the next measurement. Per GP care, participants in the control group will receive care as usual, which is mostly initiated by patient request and is usually complaint-driven. At the end of this study, the researchers will actively inform and encourage control group participants to finally use the online CAG intervention. Study groups will have full access to other interventions during the trial, but only on their initiative. The use of cointervention will be assessed by questionnaires at all time points.

### Measurements

All participants will be asked to complete an online questionnaire at baseline, 6 months, and 12 months after baseline. GPs and PNs will not be present during the self-report questionnaire (participants will complete this assessment digitally at home). Therefore, no influence of the GP or PN on the Patient Reported Outcome Measures is expected. The questionnaires will measure self-reported lifestyle behaviors, behavioral determinants, and experienced psychological problems (see the *Outcomes* section).

The second questionnaire, administered 6 months after baseline, will also include items measuring health-related costs and, for intervention group participants only, a process evaluation questionnaire. In addition, biomedical measurements will be taken from all participants at 6 months after baseline. Blood pressure, total cholesterol/high-density lipoprotein cholesterol, and blood glucose were originally planned for the biomedical measurement. However, due to current circumstances in Dutch primary care (see the *Discussion* section), total cholesterol/high-density lipoprotein cholesterol and blood glucose measurements will be discontinued in consultation with the funding agency.

Nonresponse will be prevented by using previously effective protocols, including automated reminders 1 week and again 3 weeks after the distribution of questionnaires to patients [7,21] and email reminders to GPCs to ensure blood pressure measurement at 6 months. The quality control procedures ensure that there will be little nonresponse [8-11]. To improve the engagement of GPCs, relationships will be maintained through regular emails or phone calls to the designated contact person. In addition, a Christmas card will be sent each year on behalf of the research team. In addition, the GPCs will be offered support in patient selection and patient contact by a researcher on several occasions during this study.

### Outcomes

#### Overview

The primary outcomes of this study are changes in lifestyle behaviors, measured by validated self-report questionnaires. PA will be assessed using the self-report Short Questionnaire to Assess Health [22,23]. Smoking behavior will be assessed using a validated (self-report) abstinence scale [24,25]. Alcohol consumption will be measured using a standardized alcohol consumption scale [26]. Dietary behavior will be assessed using a food frequency questionnaire on saturated fat intake and fruit and vegetable consumption [27-29].

Secondary outcomes are changes in experienced psychosocial problems such as anxiety and depression, fatigue, health-related QoL, and health-related costs, which will be assessed using validated self-report questionnaires. Anxiety and depression will be assessed using the Hospital Anxiety and Depression Scale [30,31]. Fatigue is assessed using the Checklist Individual Strength [32,33]. Health-related QoL is measured using the abbreviated European Organisation for Research and Treatment of Cancer Quality of Life Questionnaire [34,35]. Health-related costs are considered from a societal perspective and are measured as health care consumption in the last 3 months using the Institute for Medical Technology Assessment Medical Consumption Questionnaire, productivity losses in the last 4 weeks for both paid and unpaid labor using the Institute for Medical Technology Assessment Productivity Cost Questionnaire, and quality-adjusted life years (QALY) using the EQ-5D-5L [25,36-42]. All questionnaires used are validated, we do not conduct additional validation research as part of this research project.

Secondary outcomes are also blood pressure measurements, taken from all participants at 6 months postbaseline. Blood pressure will be assessed by clinical measurements performed by GPP.

In addition to outcome measures, relevant medical data (type of cancer, time since diagnosis, type of treatment, and recurrence) and social demographics (age, sex, level of education, income, living situation, comorbidities, and BMI), as well as intention toward PA, healthy diet, reduced alcohol consumption, and smoking cessation will be assessed at baseline. Items assessing recurrence, use of cointerventions, BMI, and lifestyle behavioral intentions will be repeated at the 6-month measurement and 12-month assessments.

In addition, the process evaluation will be measured by (1) dose delivered: the number of intended modules accessed; (2) dose received: the extent to which participants actively engage with the material in the module; (3) satisfaction with the program; (4) practice-patient interaction: perceptions of the level of collaboration, satisfaction, and active engagement with the blended care program; and (5) context: aspects of the environment that influenced program implementation, impact, or outcomes. In addition to self-report measurements, log data from the online CAG (use of the website and individual CAG modules) will be automatically collected throughout the intervention.

Process evaluation will also take place with GPs and PNs. During the interview session at the end of the trial, they will be asked to report on (1) their satisfaction with the blended care program; (2) the type of patients involved; (3) the number of consultations carried out by the GP or PN; (4) the practice-patient interaction: perceptions of the level of cooperation, satisfaction, and active engagement with the program; and (5) the context: aspects of the environment that influenced the implementation/impact or outcomes of the program.

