#### Sample Size

The effect evaluation of the online CAG intervention showed small to medium effect sizes (ES=0.20-0.40) on lifestyle behaviors at 6 months. In the current design, we expect an ES of 0.40 at 6 months follow-up [8]. Based on previous research on computer-tailored lifestyle interventions, we estimate an ES of 0.30 at 12 months [8,43-48]. Based on CAG data and other research in the primary care setting [49], we estimate an intracluster correlation of 0.03 to account for the multilevel design. Sample size calculation (ES=0.30; power=0.80; intracluster correlation=0.03, design effect 1.27) indicates that 282 participants are required for the effect study (141 in each condition). From 2 previous RCTs of online lifestyle interventions in patients or survivors of cancer, we know that dropout is 20%-25% [8,48]. Accounting for a 25% dropout, 376 survivors of cancer need to start in the RCT (188 per condition).

Furthermore, based on cancer prevalence figures, cancer survival rates, and the number of GPCs in the Netherlands, we expect that a standard GPC (consisting of 1-4 GPs and additional PNs) will have at least 20-40 survivors of cancer who meet the inclusion criteria. Therefore, to achieve a sufficient sample size, we aim to recruit approximately 40 GPCs, each of which will recruit 10 participants.

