### Statistical Methods

#### Overview

The first 2 steps of the analysis will test for statistical differences at baseline in lifestyle behaviors, QoL, demographics, and psychosocial and medical symptoms between the 2 study groups. Blinding of the analyst will be applied for primary outcomes. Patterns and mechanisms of missing data will be explored. Thereby, special attention will be paid to dropouts. Randomization of the GPCs should account for an even distribution between the experimental and control conditions of socioeconomic factors or other confounding factors that may skew our results. However, in case conditions are unbalanced, these factors will be adjusted for in the analysis. If necessary, other statistical adjustment procedures will be applied to minimize the impact of any bias.

Multilevel linear regression analyses will be conducted to test for differences in residual change scores between the intervention and control groups on the primary and secondary outcomes at the 6-month follow-up and the 6- and 12-month follow-up combined. Intention-to-treat (ITT) analyses with multiple imputations will be applied. Participants will be nested within GPCs to account for potential interdependence between participants. Multilevel linear regression analyses with a random intercept for GPC level will be performed to account for possible interdependence in the effect analyses. The effects on the population will be assessed via CIs.

The primary outcome measures will be the residual change scores in lifestyle behaviors, but also differences in the secondary outcomes (anxiety and depression, fatigue, [health-related] QoL, and health-related costs). Blood pressure at 6 months will be compared between the intervention and control groups. In addition, moderation analyses will be conducted to examine different potential moderators such as age, gender, type of treatment, and level of education [8-11]. Subanalyses may be performed to explore individual differences that may be attributed to the degree of participation in the intervention. Besides factors on the level of participants, factors on the level of GPCs will be considered for further analysis. Finally, process evaluation data will be analyzed and summarized descriptively.

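### The single linear residual-change model over all participants does not show whether the intervention helps smokers quit, and the stated power does not carry over to smoking

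*Protocol article*

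**What the plan says.** The Outcomes section of the protocol article states: "The primary outcomes of this study are changes in lifestyle behaviors, measured by validated self-report questionnaires". Smoking is listed there beside physical activity, alcohol and diet, with this measure: "Smoking behavior will be assessed using a validated (self-report) abstinence scale". The scoring of that scale is not given.

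The Statistical Methods section (Overview) names one model for all outcomes: "Multilevel linear regression analyses will be conducted to test for differences in residual change scores between the intervention and control groups on the primary". That sentence goes on to cover the secondary outcomes as well. The section adds: "Multilevel linear regression analyses with a random intercept for GPC level will be performed". It then repeats the rule for the primary set: "The primary outcome measures will be the residual change scores in lifestyle behaviors". No exception is made for smoking, and no set of baseline smokers is defined. On the population it says: "Intention-to-treat (ITT) analyses with multiple imputations will be applied".

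The six inclusion criteria under Recruitment of Participants do not mention smoking, so non-smokers enter the smoking analysis. Sample Size gives one calculation for lifestyle behaviours in general: "Sample size calculation (ES=0.30; power=0.80; intracluster correlation=0.03, design effect 1.27) indicates that 282 participants are required for the effect study".

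**The concern.** Someone who does not smoke at baseline cannot quit. In the smoking analysis that person can change only by taking up smoking or relapsing. A linear model over everyone therefore averages any effect on quitting over people who had nothing to quit. The intervention contains a smoking cessation module, so the clinical question is whether smokers stop. The planned coefficient does not answer it.

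The second risk is how a null result would be read. Smoking is a declared primary outcome, and the only power statement in the article is 0.80 for a standardised effect of 0.30. A reader could apply that figure to smoking and take a null result as evidence that the intervention does not help smokers. The article expressly names the model, so this is more than a detail left to a fuller plan.

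**Working it through.** **The plan's own figures.** The design effect reproduces: 1 + (10 − 1) × 0.03 = 1.27. So does the starting number: 282 / 0.75 = 376. The 282 does not follow directly from the stated inputs. With an assumed two-sided alpha of 0.05, an effect size of 0.30 needs 175 per arm, and 175 × 1.27 rounds up to 223 per arm, or 446 in all. An unstated baseline correlation of about 0.6 would bring this to 282. That is a separate matter; 282 is taken as given here.

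**Assumptions that the documents do not supply.** Smoking scored abstinent or not; 5% to 20% smokers at baseline (p); quitting 10% under usual care and 30% with the intervention; 1% uptake among non-smokers in both arms.

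**What the coefficient estimates.** With quit rates q1 and q0 and uptake rates u1 and u0, the arm difference in abstinence given baseline status is

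p × (q1 − q0) − (1 − p) × (u1 − u0).

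With equal uptake this is p × 0.20.

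**Standardised size.** Within an arm, the variance given baseline status is p × q × (1 − q) + (1 − p) × 0.01 × 0.99. At p = 0.10:

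- control: 0.10 × 0.09 + 0.90 × 0.0099 = 0.01791
- intervention: 0.10 × 0.21 + 0.90 × 0.0099 = 0.02991
- mean 0.02391, SD 0.155, standardised effect 0.02 / 0.155 = 0.13

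| Baseline smokers | Of 282 | Of 127 | Whole-sample difference | SD | Standardised effect |
|---|---|---|---|---|---|
| 5% | 14 | 6 | 1 point | 0.130 | 0.08 |
| 10% | 28 | 13 | 2 points | 0.155 | 0.13 |
| 15% | 42 | 19 | 3 points | 0.176 | 0.17 |
| 20% | 56 | 25 | 4 points | 0.195 | 0.21 |

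Even a tripled quit rate stays below 0.30 throughout.

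**Power and test size.** These come from simulation of a linear model adjusted for baseline smoking over all participants, without clustering, as a stand-in for the residual-change analysis. The smaller size is 126 rather than 127, so that the arms are equal.

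- At 282, power for 10% versus 30% quitting is about 9% to 40% across 5% to 20% smokers. For 10% versus 25% it is 6% to 27%.
- At 126, power for 10% versus 30% is about 5% to 19% (a repeat run put the lower end at 4%).
- With no true effect, rejection is about 4% to 5% at 282 and 1% to 3% at 126. At 126, about 2% to 16% of null data sets had no usable variation.

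**How much is due to the model.** A non-exact comparison among smokers only, under the same assumptions at 282, has power of about 11% to 45%, modestly better than 9% to 40%. Fisher's exact test gains nothing: 14% to 26% with 14 to 21 smokers per arm, where the linear model has about 18% to 28%.

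**The case against.** The strongest reply is that the two facts carrying the point are not in the documents. The article does not show how the abstinence scale is scored, and it gives no smoking prevalence. Both are therefore stated as assumptions with a range. A graded score would change the model question, but non-smokers would still have almost no room to change, so the dilution would remain.

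Several stronger readings are tempting and do not hold.

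- A reader might infer that the linear test yields false positives. It does not: it is near nominal at 282 and conservative at about 95 to 126.
- A reader might blame the model for all the lost power. Most of it comes from having few smokers, and restricting the analysis to them recovers only a little.
- A reader might take the small-sample case as 127 less 25%, about 95. The plan specifies multiple imputation, so all enrolled participants enter the analysis. The 127 is itself a December 2024 count.
- A reader might say that the plan claims 80% power for smoking. It makes one generic calculation and no claim specific to smoking. Planned confidence intervals and Bayes factors could also show that the evidence is inconclusive. The fault is that the limit of the power statement is not declared.

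It is also fair that a whole-sample contrast is a legitimate estimand and keeps relapse in view; the Economic Evaluation section uses maintenance of a healthy lifestyle as an effect. That stands, provided the contrast is not presented as an effect on quitting. Moving smoking to the secondary outcomes near the end of data collection would be debatable and is not needed.

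**Conclusion.** The point holds in this limited form. The article sets a linear residual-change model over all participants for a primary outcome measured by an abstinence scale, in a sample not selected for smoking. The result would be a quitting effect scaled down by smoking prevalence and mixed with uptake and relapse. Under the stated assumptions, the standardised effect for a tripled quit rate is about 0.08 to 0.21 against the planned 0.30, so the planned power does not apply to smoking at 282 and still less at the recruited size. The harm is to interpretation and to the reach of the power statement. The exact figures depend on assumed prevalence, quit rates and uptake, and on a simulation without clustering.

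**What to change.** In Statistical Methods, exempt smoking from the linear residual-change model and state how the scale is scored. If it is abstinent or not, analyse abstinence at follow-up among baseline smokers with a mixed logistic model, Firth-penalised if quitters are few. Keep the multiple imputation. Report counts of smokers and quitters by arm, and report relapse or uptake among baseline non-smokers alongside. The penalised model's power was not evaluated here, and it should not be presented as a cure for scarce smokers.

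In Sample Size, state that the calculation with effect size 0.30 and power 0.80 covers the continuous behaviours only, and that the smoking result will be imprecise.

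Smoking can remain primary. The cost is a change of wording, dated and made before the smoking outcome is analysed by arm. The downside is a wide, openly reported interval for smoking.
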